## Abstract

**Background:**

Despite improvements in surgical as well as adjuvant therapies over the last decades, the prognosis for patients with glioblastoma remains poor. Five-Aminolevulinic acid (5-ALA) induced porphyrins are already used for fluorescence-guided resection and as photosensitizer for photodynamic therapy. New findings reveal their potential use as sensitizing agents in combination with ionizing radiation.

**Methods:**

We initiated a phase I/II dose escalation study, treating patients with recurrence of glioblastoma with oral 5-ALA concurrent to radiotherapy (RT). This prospective single-center study based in the University Hospital Münster aims to recruit 30 patients over 18 years of age with histologically verified recurrence of supratentorial glioblastoma in good performance status (KPS ≥ 60). Following a 3 + 3 dose-escalation design, patients having undergone re-resection will receive a 36 Gy RT including radiodynamic therapy fractions (RDT). RDT constitutes of oral administration of 5-ALA before the irradiation session. Two cohorts will additionally receive two fractions of neoadjuvant treatment three and two days before surgery. To determine the maximum tolerated dose of repeated 5-ALA-administration, the number of RDT-fractions will increase, starting with one to a maximum of eight fractions, while closely monitoring for safety and toxicity. Follow-up will be performed at two and five months after treatment. Primary endpoint will be the maximum tolerated dose (MTD) of repeated ALA-administration, secondary endpoints are event-free-, progression-free-, and overall-survival. Additionally, 5-ALA metabolites and radiobiological markers will be analysed throughout the course of therapy and tissue effects after neoadjuvant treatment will be determined in resected tissue. This protocol is in accordance with the SPIRIT guidelines for clinical trial protocols.

**Discussion:**

This is the protocol of the ALA-RDT in GBM-study, the first-in-man evaluation of repeated administration of 5-ALA as a radiosensitizer for treatment of recurrent glioblastoma.

**Trial registration:**

This study was approved by the local ethics committee of the Medical Association of Westphalia-Lippe and the University of Münster on 12.10.2022, the German federal institute for Drugs and medical devices on 13.10.2022 and the federal office for radiation protection on 29.08.2022. This trial was registered on the public European EudraCT database (EudraCT-No.: 2021-004631-92) and is registered under www.cliniclatrials.gov (Identifier: NCT05590689).

## Background

Glioblastoma multiforme is the most common malignant brain tumor in adults. Infamous for its poor prognosis, treatment of this highly lethal, primary brain malignancy traditionally includes resective surgery (if possible) and postoperative chemoradiation. Based on the findings of Stupp et al., the current standard of adjuvant therapy is 60 Gy of fractioned radiation treatment (RT) to a locally extended tumor site with concurrent and adjuvant application of oral temozolomide [1]. Modern radiotherapy benefits from technical and conceptual innovations like image-guided and intensity modulated treatment.

Nevertheless, recurrence seems to be inevitable for patients with glioblastoma, mainly located in or adjacent to the initial tumor site. As of today, clear treatment standards are still missing in cases of relapse or progression [2]. Re-resection and re-irradiation are treatment options in this situation [3–7], oftentimes combined with concurrent or sequential second line chemotherapy, target therapy or monoclonal antibodies, but treatment use is oftentimes limited due to prior therapy.

Multiple study approaches have aimed to increase the effectiveness of local re-treatment and re-irradiation for recurrent glioblastoma patients, attempting to achieve a more potent, more precise, and overall more effective adjuvant treatment [8–17]. In this regard, the use of radiosensitizers as a means of improving local therapy outcome by increasing effectiveness of adjuvant RT has been explored in several forms but results mostly did not match expectations and failed to improve survival when compared to standard treatment [18]. Nevertheless, new treatment agents and regimen are evaluated constantly, based on the increasing understanding of the complex characteristics and behavior of this tumor entity [11, 19–21].

Five-Aminolevulinic acid (5-ALA), a ketone carbon amino acid, has already proven to be of significant value in the treatment of glioblastoma: increasing tumor visibility under fluorescent light, based on selective uptake and production of fluorescent and photoactive porphyrins in glioma cells, surgical resection can be improved, leading to a significant increase in survival [22]. Furthermore, its application as a photoactive substance shows potential in the context of photodynamic therapy (PDT) when exposed to light of a certain wavelength (23, 24). Unfortunately, this procedure is complex, and its scope may be limited due to the restricted light penetration of brain tissue. Recent in-vitro-studies have revealed the cytotoxic effect (similar to PDT) to also be inducible by exposure of cells containing the metabolite Protoporphyrin IX (PPIX) to ionizing radiation, resulting in increased cell damage, based on a delayed mitochondrial production of reactive oxygen-species (ROS) (25, 26). While this has been evaluated in several preclinical settings for different tumor entities [27–30], no studies involving humans have evaluated the concept of repeated application of 5-ALA during the course of fractioned RT yet. When compared to other radiosensitizing agents, 5-ALA seems to have an advantage due to its tumor-selective behavior deriving from its active uptake into glioma cells via specific transporters [31–33] after extravasation and distribution along the infiltration zone by local edema [34]. Combined with the overall low toxicity (known from its well implemented use in resective surgery) and easy handling via oral application, 5-ALA appears to be a strong contender to improve therapy effectiveness without immoderate risk of increasing side effects. In this article, a description of our protocol for the recently initiated “ALA-RDT in GBM” 3 + 3 dose escalation trial is given, aiming to further explore the potential of this promising combination.

## Methods

### Trial design, setting and recruitment

This is a prospective, single-armed, single center phase I/II dose escalation-study, based in the University Hospital of Münster, Germany. The aim of the study is to determine the maximum tolerated dose (MTD) and safety of repeated application of oral 5-ALA as a radiosensitizer during (neo)adjuvant radiotherapy for the treatment of glioblastoma recurrence. All patients will receive 36 Gy adjuvant RT in 20 fractions. An increasing number of RT-fractions will be conducted as radiodynamic therapy (RDT), which will consist of 1.8 Gy-irradiation 7–9 h after oral application of 20 mg/kg bodyweight 5-ALA in a tap-water-solution.

Recruitment will start in cohort 0 with one RDT-fraction and patients will be allocated consecutively to this and the following cohorts, which will be numbered sequentially from 0 to 8. Each cohort encompasses three initial patients being expanded by additional three participants in case of a dose limiting toxicity (DLT), following a 3 + 3-design. With increasing cohort number, the quantity of RDT-fractions will be increased by one with a maximum of eight adjuvant applications in cohort 8. Additionally, in cohorts 0 and 1, patients will receive two neoadjuvant RT-fractions (in case of cohort 1, the first fraction will be conducted as RDT). In these cohorts, a decisive histopathological analysis of the resected tissue will account for changes induced by neoadjuvant therapy. MDT is considered to be reached in case of DLT in two or more patients on the same dose level. A study continuation with the next dose-level will be evaluated and approved by the data safety and monitoring board (DSMB) after a six-week follow-up of the last RT-fraction of the last patient within a cohort. The study started recruitment with the first patient in Q1 2023 with an estimated study duration of 30 months.

### Study population

26 patients will be recruited with additional 15–20% drop-outs, cumulating in approximately 30 patients. End of study is defined as the last patient’s last visit (six-month follow-up). For each drop-out, a new patient will be entered into the study at the same dose level.

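### The stated 26 patients (about 30 with drop-outs) fall below the 27 evaluable patients that the plan's own nine-cohort rule needs with no DLT, and leave no room for expansion

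*Protocol article*

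**What the plan says.** Three parts of the protocol article bear on the size of the trial.

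- **Size.** Study population: "26 patients will be recruited with additional 15–20% drop-outs, cumulating in approximately 30 patients". The Methods paragraph of the abstract says that the study "aims to recruit 30 patients over 18 years of age". Study population adds: "For each drop-out, a new patient will be entered into the study at the same dose level".
- **Cohort rule.** Trial design, setting and recruitment describes cohorts "which will be numbered sequentially from 0 to 8". It continues: "Each cohort encompasses three initial patients being expanded by additional three participants in case of a dose limiting toxicity (DLT"). The MTD counts as reached with "DLT in two or more patients on the same dose level". Table 2 lists all nine cohorts.
- **Time.** The same section lets the DSMB approve the next level only "after a six-week follow-up of the last RT-fraction of the last patient within a cohort". It describes a study "with an estimated study duration of 30 months". Study population ends the study at the last patient's six-month visit.

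The article states no DLT rate, number of expansions or accrual rate.

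**The concern.** The size and the cohort rule are both stated, and they do not agree. Nine cohorts of three make 27, and the plan says 26. The difference is only one patient, but 26 is not a multiple of three, so no sequence of full cohorts of three or six produces it. Leaving out cohort 0 gives 24, which does not explain it either.

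The larger gap is that the figure contains nothing for the expansions that the same section requires. The MTD is the primary endpoint. If recruitment or time ended the ladder, the highest level reached could be read as an MTD although toxicity had not set it.

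**Working it through.** **1. The plan's own figure.** 26 × 1.15 = 29.9 and 26 × 1.20 = 31.2, so about 30 reproduces at the lower end of the drop-out range. The 26 itself does not follow from the cohort rule.

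**2. Evaluable patients needed to clear cohort 8.**
- No DLT: 9 × 3 = 27.
- One level expanded: 27 + 3 = 30. Two levels: 33.
- All nine expanded: 9 × 6 = 54.

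**3. Enrolment, with drop-outs replaced at the same level.** Enrolled = evaluable / (1 − drop-out), rounded up.
- 27 evaluable: 27/0.85 = 31.8 and 27/0.80 = 33.8, so 32–34.
- 30 evaluable: 30/0.85 = 35.3 and 30/0.80 = 37.5, so 36–38.
- Each expanded level: 3/0.85 = 3.5 to 3/0.80 = 3.8.
- In the other direction, 30 enrolled leave 30 × 0.85 = 25.5 or 30 × 0.80 = 24. They leave 27 only if drop-out is 1 − 27/30 = 10% or less.
- If the 15–20% is instead a share added to the evaluable number, 30/1.15 = 26.1 and 30/1.20 = 25. That is still below 27.

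**4. Chance that 30 enrolled resolve the ladder.** Resolved means either that an MTD is found or that cohort 8 is cleared. Assumptions: the same DLT risk p for every patient at every level; independent drop-out; drop-outs not counted for DLT; no further patients once two DLTs occur at a level. With q = 1 − p, a level of three has:
- no DLT with probability q³, and the ladder moves up;
- one DLT with probability 3pq², and three more are treated; the ladder moves up if none of these has a DLT (q³) and otherwise stops;
- two or more DLTs otherwise, and the ladder stops.

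This gives the exact distribution of the number N of evaluable patients used. Each value of N is then weighted by the binomial chance that 30 enrolled yield at least N evaluable.

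| Assumed DLT risk | Mean N evaluable, no limit on enrolment | Resolved within 30 enrolled (20% to 15% drop-out) |
|---|---|---|
| 0% | 27.0 | 12–32% |
| 2% | 28.0 | 10–22% |
| 5% | 27.6 | 19–25% |
| 10% | 23.4 | 45–48% |
| 20% | 13.6 | 85–87% |

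Among ladders that clear cohort 8, the mean N is 30.2 at 5% and 32.3 at 10%.

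**5. Duration with no DLT.** Inputs: 20 fractions at five per week (25 days to 4 weeks); six weeks' observation; for cohorts 0 and 1, three days before surgery plus 2–6 weeks from surgery to adjuvant RT; six months from the last patient's first adjuvant fraction (26.1 weeks). All three patients of a cohort are taken to start together.
- Shortest: 8 × (3.57 + 6) + 2 × (0.43 + 2) + 26.1 = 76.6 + 4.9 + 26.1 = 107.5 weeks, or 24.7 months.
- Longest: 8 × (4 + 6) + 2 × (0.43 + 6) + 26.1 = 80 + 12.9 + 26.1 = 118.9 weeks, or 27.4 months.
- Left from 30 months: 2.6–5.3 months for all screening, accrual and DSMB review, which is about 1.3–2.5 weeks per cohort.
- Each expansion adds at least 9.57–10 weeks (2.2–2.3 months) if the extra patients start after the first three have been observed.

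**The case against.** The strongest reply is that 27 is the floor only for the full ladder. A 3+3 that meets two DLTs at a lower level has answered its question with fewer patients; at a flat 10% risk the mean is 23.4 evaluable. This stands. A reader might count only ladders that clear cohort 8 and quote a 3–8% chance of success within 30 enrolled at 5% DLT risk. That treats valid stops at an MTD as failures. The any-route figures in the table are the fair ones.

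A reader might also infer that 30 is a cap and that the MTD would reflect it. The article says approximately 30, replaces drop-outs and requires expansion, and it states no rule that stops enrolment at 30. The risk to the MTD is therefore conditional on such a rule.

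On the no-DLT path the shortfall falls mainly on cohort 8. The chance that 30 enrolled yield the 24 evaluable patients for cohorts 0 to 7 is 85% at 15% drop-out and 61% at 20%.

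Multiplying by 1.15 instead of dividing by 0.85 is a minor matter of about one patient. A full derivation under several DLT curves may belong in documents not shown, and its absence is not criticised here. What remains is that the stated number and the stated cohort rule disagree within one article.

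**Conclusion.** The point holds as a mismatch between the stated size and the stated design. The gap is one patient on the no-DLT path before drop-outs. Against about 30 enrolled it is 2–4 patients (32–34 needed), and it grows by three evaluable patients with each expanded level.

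The any-route chances rest on flat DLT risks that are assumptions. They are lowest, at 10–32%, for risks of 0–5%. That is the range nearest to the Background and Discussion, which describe 5-ALA as well tolerated in surgical use, although the Discussion leaves cumulative toxicity open. At 20% risk the stated size is usually enough.

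The duration is a secondary point. A reader might conclude that 30 months is impossible, but the documents do not support that, because the procedural minimum is about 25–27 months. What they show is little slack: about 3–5 months for all screening, accrual and review at one center, with room for at most one or two expansions even if patients are available almost at once.

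**What to change.** Reconcile the abstract, Trial design, setting and recruitment, and Study population as follows:

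- State the size as 27 evaluable patients with no DLT (about 32–34 enrolled at 15–20% drop-out), plus about 3.5–3.8 enrolled for each expanded level, up to 54 evaluable. Name the number of expansions allowed for in the planning figure.
- Restate the duration on the same basis, with the accrual rate assumed.
- State that about 30 is not a cap. If it is a cap, state that a ladder ended by enrolment or time is reported as MTD not reached up to level k, and not as an MTD.

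The cost is less favourable planning figures and an amendment or notification. The escalation rule and the study procedures do not change.

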### Inclusion criteria

1: Written patient consent after comprehensive information.

2: Age ≥ 18 years.

3: Recurrence of supratentorial glioblastoma after initial resection and adjuvant therapy.

(e.g. radio-chemotherapy, targeted therapies, antiangiogenic therapies as determined.

by the tumor board) (with planned second resection cohort 0 and 1), second or third.

recurrences permitted.

4: Clinically indicated further radiotherapy as per decision of the tumor board as part of.

therapy for recurrence.

5: Histological verification of recurrent glioblastoma independent of methylated MGMT.

promotor status when alkylating chemotherapy failed at this time.

6: Karnofsky Performance Score ≥ 60.

7: For all patients of reproductive potential: Willingness to apply highly.

effective contraception (Pearl index < 1) during the entire study (and for at least 6.

months after the last application of 5-ALA)

8: Pre-menopausal female patients with childbearing potential: a negative serum pregnancy test must be obtained max. 72 h prior to treatment start.

9: Adequate liver function: bilirubin < 1.5 times above upper limit of normal range (ULN), alanine transaminase (ALT/SGPT) and aspartate transaminase (AST/SGOT) < 3 times ULN. In the case of documented or suspected Gilbert’s disease bilirubin < 3 times ULN.

10: Adequate renal function: creatinine < 3 times above ULN; eGFR >/= 60 ml/min, Blood clotting: INR/Quick/PT and PTT within acceptable limits according to the investigator.

### Exclusion criteria

1: Patient unable to undergo imaging by MRI, PET or contrast-enhanced CT for whatever reason (e.g. pacemaker).

2: Pregnant or breastfeeding women.

3: Past medical history of diseases with poor prognosis, e.g., severe coronary heart disease, heart failure (NYHA III/IV), severe and poorly controlled diabetes, immune deficiency, residual deficits after stroke, severe mental retardation or other serious concomitant systemic disorders incompatible with the study (at the discretion of the investigator).

4: Any active infection (at the discretion of the investigator).

5: Hypersensitivity against porphyrins.

6: Known diagnosis of porphyria.

7: Current participation in another clinical trial with therapeutic intervention or use of any other therapeutic interventional agent other than the standard therapy since diagnosis of glioblastoma.

8: Known intolerance to study medication.

9: Pre-treatment with other potentially phototoxic or photosensitizing substances (e.g. tetracyclines, sulfonamides, fluoroquinolones, hypericin extracts, products containing St. John’s wort) during the two weeks preceding RDT.

### Treatment procedures

#### Radiation treatment

The indication for second irradiation will be discussed and decided in the multidisciplinary tumor board before the screening process. Adjuvant radiotherapy will consist of fractioned photon irradiation, delivering a total dose of 36 Gy in 20 fractions, with five fractions applied per week (Monday through Friday). In cohorts 0 and 1, patients will receive two additional fractions of 1.8 Gy as neoadjuvant treatment, resulting in a cumulative dose of 39.6 Gy. Target definition and dose prescription will be according to ICRU 83 (for intensity-modulated radiotherapy) and planned with dedicated computed tomography (CT), pre- and postoperative contrast-enhanced MRI and three-dimensional planning systems. Gross tumor volume (GTV) will be defined in the pre- and postoperative MRI as the extend of the contrast-enhancing T1-hyperintense tumor site, the clinical target volume (CTV) will consist of a 1 cm margin around the GTV, also considering additional imaging (if available), respecting anatomical borders, and considering pre-treatment dose distributions. The planning target volume (PTV) will be defined as a 0.3–0.5 cm margin around the CTV. Dose constraints will be considered according to QUANTEC-recommendations. Intensity-modulated radiotherapy will be delivered with linear accelerators with a beam energy of 6 MV or 6 MV FFF, quality assurance will be performed by means of individual case reviews and image-guidance via frequent cone beam CT.

Preoperative irradiation will be performed in two fractions; one fraction daily, three and two days before the scheduled operative resection. Postoperative irradiation will begin after clinical recovery two to six weeks (as clinically indicated) after surgery.

#### Drug administration

Oral 5-Aminolevulinic acid will be applied on RDT-treatment days as a solution in tap water with a dose of 20 mg/kg bodyweight between seven and nine hours prior to 1.8 Gy-irradiation. Additionally, patients will receive 5-ALA four hours prior to induction of anesthesia for surgery. Use of additional concomitant chemo- or immunotherapy is prohibited during trial participation.

#### Blood and tissue samples

Tissue sampling and evaluation of morphological changes in brain tissue will be performed on cohorts 0 and 1 after neoadjuvant treatment. These analyses will therefore include tissue changes after sole RT (cohort 0) as well as RDT (cohort 1), based on parameters like Caspase-3, IBA1, H&E, EvG, P53, Ki67 and gammaH2AX. Blood samples will be drawn for safety clearance as part of toxicity assessment and to monitor changes of ALA-metabolites in serum (PPIX) before every application of 5-ALA. Additional blood samples for analysis of concentration changes in radiobiological markers (including markers like IL-6, IL-8, TNF-Alpha and VEGF) will be drawn during neoadjuvant treatment (day − 3 and day − 2) and at the beginning (day 1 and day 2) and end (day 20) of adjuvant treatment.

Concentration changes of 5-ALA-metabolites in urine samples will be evaluated during neoadjuvant treatment (day − 3) and surgery (day 0) for cohorts 0 and 1 and at the beginning (day 1) and first follow-up for all study participants.

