### Toxicity assessment

All patients will be hospitalized for the course of treatment procedure and receive daily AE/SAE-monitoring. Physical and neurological examinations will be performed routinely on a weekly basis and laboratory panels for toxicological safety will be drawn before every RDT-fraction, but also at least weekly. Toxicity will be monitored daily and classified according to CTCAE Vers. 5.0. All serious adverse events will be immediately reported to the Data Safety Monitoring Board.

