### End-points

Primary: To determine the maximum tolerated dose and safety of (neo)adjuvant RDT. MTD is defined as maximum dose level before two or more patients suffer from DLT.

Secondary: To evaluate six-months overall survival rate (OSR), six-months progression-free survival rate (PFSR) and six-months event-free survival rate (EFSR), as well as histological tissue changes after neoadjuvant treatment. OSR, PFSR and EFSR will be determined from study inclusion to the second follow-up, six months after the beginning of adjuvant treatment.

Exploratory: To explore concentration changes of 5-ALA metabolites in urine samples and changes of radiobiological marker concentration in blood serum samples.

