### Statistical analysis

Statistical analyses will include “intention-to-treat”-evaluation for all cohorts’ primary and secondary endpoints and “per-protocol”-evaluation for explorative endpoints. “Per protocol” is defined as administration of RT- and 5-ALA-applications according to prescribed dose. Descriptive measures for all variables will be given. Rates of adverse events will include all events qualifying for CTCAE grade 3 or greater and the final DLT-rate will be estimated by use of the Bayesian Time-to-Event Continual Reassessment Method (Tite-CRM). Survival parameters will be analyzed using the Kaplan-Meier method and two-sided log-rank tests for comparative analyses between defined subgroups. Cox regression testing will estimate impact of risk factors (e.g. age, KPS, gender) on these parameters.

All data will be compared to historical data using the Mann-Whitney U test, Fisher’s exact test, or Chi² test.

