## Discussion

The treatment of recurrent glioblastoma lacks clear standards with re-resection, re-irradiation and systemtic agents being the pillars of therapy. A recent phase II trial (RTOG1205, [35]) has demonstrated a PFS-benefit when combining salvage therapy (in the form of bevacicumab) with re-RT. Nevertheless, second treatment of all modalities oftentimes suffers from limitations and improvements of therapy effectiveness are needed. Based on the well-established use of 5-ALA for surgery of glioblastoma [22, 36–38] and promising preclinical data [27–30], this study aims to answer the question if the addition of repeated applications of oral 5-ALA during re-irradiation is safe and may be beneficial towards survival parameters. While several other agents did not result in improvement of outcome [18], the use of 5-ALA as a radiosensitizer is especially promising because of the selective uptake in glioma tumor cells, sparing normal brain tissue [34, 39]. Moreover, 5-ALA is easy to apply and generally tolerated well, for example in the context of surgery and PDT. We chose to design this trial in the setting of recurrent glioblastoma, based on the high need for effective salvage treatment options in this patient cohort and the lack of a clear treatment standard. In case of positive results, further evaluation as an addition to standard first line treatment may be attempted.

However, no data is available regarding consecutive applications of the drug yet. In the context of brain tumor surgery single doses of up to 60 mg/kg have previously been reported to be well tolerated [40], so that a dose escalation trial using 20 mg/kg increments appears to be justified.

Despite that fact, cumulative effects resulting in hepatotoxicity or increased photosensitivity from repetitive applications cannot be ruled out. The blood and urine samples collected during the study aim to understand instances of drug- or metabolite-accumulation and to prevent them in the future.

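### In cohorts 2 to 8 the exploratory urine endpoint cannot show metabolite build-up during repeated 5-ALA dosing, and its per-protocol set leaves out patients who stopped 5-ALA early

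*Protocol article*

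**What the plan says.** Under End-points, the exploratory aim begins "To explore concentration changes of 5-ALA metabolites in urine samples" and goes on to radiobiological markers in serum. Serum PPIX appears in no endpoint class.

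Under Blood and tissue samples, urine is collected "during neoadjuvant treatment (day − 3) and surgery (day 0) for cohorts 0 and 1", and then "at the beginning (day 1) and first follow-up for all study participants". The second rule is the only one that applies to cohorts 2 to 8. Blood is drawn "to monitor changes of ALA-metabolites in serum (PPIX) before every application of 5-ALA", without restriction to particular cohorts. Marker blood is drawn on days −3, −2, 1, 2 and 20.

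The trial design section says that "the quantity of RDT-fractions will be increased by one with a maximum of eight adjuvant applications in cohort 8", and Table 2 gives the RDT days.

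Under Statistical analysis, primary and secondary endpoints are analysed by intention to treat and exploratory endpoints per protocol, which "is defined as administration of RT- and 5-ALA-applications according to prescribed dose".

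The Discussion gives the purpose: "The blood and urine samples collected during the study aim to understand instances of drug- or metabolite-accumulation". The Abstract describes metabolite analysis as spanning the whole course of therapy.

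**The concern.** A question about accumulation needs measurements while doses are being repeated. Cohorts 2 to 8 give two to eight RDT doses, but their two urine samples lie at the start of adjuvant treatment and weeks after the last dose. If metabolites rose from dose to dose and then fell again, the urine data would look the same as if they had never risen.

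The analysis set adds a second problem. Someone who stops 5-ALA early has not received it as prescribed, so the definition as worded excludes that patient from the urine and marker analyses. The Discussion names liver toxicity and photosensitivity as possible cumulative effects. If either led to stopping, the excluded patients would be those most informative about accumulation, and the remaining set would be selected for tolerance.

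At stake is whether the exploratory data can answer the question they are collected for. Dose-limiting toxicity decisions are not at stake.

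**Working it through.** The plan gives no figure to reproduce, so the check counts samples against the schedule.

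**Inputs.** RDT days come from Table 2. Radiotherapy is given Monday to Friday (Radiation treatment). Urine and PPIX rules come from Blood and tissue samples. First follow-up is either 12 weeks after the first adjuvant fraction (Table 1) or six weeks after the end of radiotherapy (Follow-Up section).

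**Assumptions.** Day 1 is a Monday and no fraction is delayed.

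**Calendar days.** Each completed five-fraction week adds a two-day weekend. Treatment days 6, 11, 16, 19 and 20 are therefore calendar days 8, 15, 22, 25 and 26.

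**Follow-up day.** Reading A (Table 1): 1 + 84 = day 85. Reading B (six weeks after radiotherapy): 26 + 42 = day 68.

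**Gaps.** Follow-up gap = follow-up day minus calendar day of the last RDT. Day-20 gap = 26 minus the same day.

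| Cohort | RDT treatment days | Last RDT, calendar day | Urine after first and up to last RDT | Gap A (days) | Gap B (days) | Pre-dose PPIX after an earlier RDT | Day-20 gap (days) |
|---|---|---|---|---|---|---|---|
| 2 | 1, 6 | 8 | 0 | 77 | 60 | 1 | 18 |
| 3 | 1, 6, 11 | 15 | 0 | 70 | 53 | 2 | 11 |
| 4 | 1, 6, 11, 16 | 22 | 0 | 63 | 46 | 3 | 4 |
| 5 | 1, 4, 6, 11, 16 | 22 | 0 | 63 | 46 | 4 | 4 |
| 6 | 1, 4, 6, 9, 11, 16 | 22 | 0 | 63 | 46 | 5 | 4 |
| 7 | 1, 4, 6, 9, 11, 14, 16 | 22 | 0 | 63 | 46 | 6 | 4 |
| 8 | 1, 4, 6, 9, 11, 14, 16, 19 | 25 | 0 | 60 | 43 | 7 | 1 |

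**Urine.** No cohort from 2 to 8 has a sample during repeated dosing. The next one comes 60 to 77 days (reading A) or 43 to 60 days (reading B) after the last dose.

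**Serum PPIX.** Pre-dose samples per patient on RDT days run from 2 to 8, which sum to 35 over the seven cohorts. With three patients per cohort that is 35 × 3 = 105. The first in each patient has no earlier RDT dose, which leaves (35 − 7) × 3 = 84 informative troughs.

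**After the final dose.** PPIX sampling is tied to the next application, so none is scheduled after the last dose or after the dose that led a patient to stop. The safety panels are more frequent ("laboratory panels for toxicological safety will be drawn before every RDT-fraction, but also at least weekly"), but PPIX is not named among them.

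**Which follow-up is first.** Table 1 labels the 12-week visit Follow-Up 1, and End-points calls the six-month visit the second follow-up. The Follow-Up section nevertheless places a six-week visit before both. Table 1 is the likelier meaning, and the result holds on either.

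**The case against.** The strongest reply is serum PPIX. The Discussion gives the accumulation question to blood and urine together, and 84 troughs at dosing intervals of 3, 4 or 7 days can show a rising pre-dose level. This stands. A reader might infer that the sampling plan as a whole cannot show accumulation, and the document does not support that. What remains is that the urine endpoint cannot, that PPIX sampling stops at the last application, and that PPIX is not listed as an endpoint.

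Second, the per-protocol rule reaches only the exploratory endpoints. Safety belongs to the primary endpoint and is analysed by intention to treat, so toxicity in early stoppers is kept. Serum PPIX has no stated analysis set, so the rule is not shown to apply to it. The serum markers, such as IL-6 and VEGF, do not measure accumulation. All this stands and limits the second limb to the urine and marker analyses.

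Third, the planned drop-outs do not size the exclusion. The document plans 26 patients plus 15–20%, which gives 26 × 0.15 = 3.9 to 26 × 0.20 = 5.2. It replaces drop-outs at the same dose level and does not say that they are incomplete 5-ALA courses.

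Fourth, the document gives no clearance time, so the follow-up urine cannot be called washed out as a fact. It also does not say whether day-1 urine precedes that day's dose, and patients receive 5-ALA before surgery as well. The conclusion needs none of these: a raised late value could show persistence, but a normal one would say nothing about levels during dosing.

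Fifth, a condensed article may omit sampling detail. Here, however, the urine days and the analysis set are stated, and the point concerns what they fix.

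**Conclusion.** The point holds in a limited form. In all seven multi-dose cohorts the urine endpoint has no observation between the first and last RDT dose, and the next comes about 6 to 11 weeks after the last (43 to 77 days over both readings of first follow-up). It cannot track build-up during repeated dosing, although the Discussion gives accumulation as a purpose of the samples. Pre-dose PPIX partly fills the gap, but it misses the state after the final dose and has no place among the endpoints. The per-protocol set, read plainly, removes early stoppers from the urine and marker analyses. How many is not known from the document.

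The maximum tolerated dose, safety and secondary endpoints are unaffected. The change is still worth making, because it is cheap and a urine sample missed during dosing cannot be recovered. The day counts assume a Monday start and no interruptions; the absence of urine during dosing does not depend on them.

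**What to change.** 1. **Urine during dosing.** Collect urine with the existing pre-dose PPIX draw at RDT visits, at least the last one, and again on day 20. Keep the follow-up sample as the late value. Day 20 alone would not do: it falls 18 days after the last RDT in cohort 2 and 1 day after it in cohort 8, so time since dose would be mixed up with dose level. Collecting at every RDT visit also covers patients who stop unexpectedly.
2. **PPIX after the last dose.** Measure PPIX in the blood already drawn on day 20.
3. **Endpoint list.** Name serum PPIX as an exploratory endpoint.
4. **Analysis set.** Analyse metabolites and markers in all patients with at least one 5-ALA dose, by number of doses received and time since the last dose. Keep per protocol as a sensitivity analysis.
5. **First follow-up.** State which visit is meant, and make Table 1, the Follow-Up section and the sampling section agree.

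Cost: with three patients in each of seven cohorts, the minimum is 21 × 2 = 42 extra urine samples. Sampling at every RDT visit after the first, plus day 20, gives 84 + 21 = 105. Patients are in hospital during treatment, so no visit is added. Some sample series will be incomplete. Recruitment has begun, so new samples can come only from patients not yet treated; items 3 to 5 change wording only.
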